#### Outcome measures

*Intervention fidelity*. Several strategies will be employed to ensure that the educational intervention is delivered faithfully. Firstly, the intervention delivery will be provided in such a way as to preserve its consistency while at the same time making sure that the participants are encouraged and reinforced in their compliance with the intervention. Consistency in the delivery of intervention is also ensured by dividing the intervention group into smaller groups. The educational intervention will be independently conducted by the researcher for each of the smaller groups. Uniform delivery of the education intervention for all subgroups can be achieved by adhering to a strict protocol. During the sessions, instant feedback can be provided to the participants by the researcher who plays the part of an observer. Intervention fidelity is also enhanced by sending regular short text messages to keep the participants’ spirits up and to ensure that they will not lapse in TB treatment adherence.

*Participant privacy*. Honesty is particularly stressed to the participants to obtain sincere responses. The participants will be informed that the questionnaires will not contain any identifying information and they will only be tagged with a unique number for identifying them later.

#### Study outcomes

*Primary outcome*. The primary outcome of interest in this study is the treatment adherence for TB medications. The data will be collected using the Medication Adherence Rating Scale (MARS), a 10-item self-reporting instrument that describes three dimensions: medication adherence behaviours (items 1–4), attitude toward taking medication (items 5–8), as well as negative side effects and attitudes to medication (items measured 9–10) [26].

*Secondary outcomes*. The secondary outcome variables in this study include:

#### Knowledge of Tuberculosis

Patients’ TB disease and treatment knowledge will be assessed using an adapted questionnaire that consists of 15 items including causes of TB, symptoms of TB, TB transmission, TB medication, and medication adherence. Permission to use the validated questionnaire from [17] has been obtained by the researchers. A nominal scale of “correct”, “incorrect”, and “I do not know” is used to measure the responses. Each correct answer is given one point while zero point is given for incorrect or “I don’t know” response. The score will range from 0 to 15.

#### Tuberculosis health belief

Next, the perception of health belief among the TB patients will be assessed using the same questionnaire [17]. Based on the six HBM domains. The modified questionnaire consists of 30 questions made up of self-reported measurement scales that represent perceived susceptibility to TB infection (three items), perceived seriousness of TB infection (six items), perceived benefits of TB medication adherence (five items), perceived barriers for TB medication adherence (eight items), confidence in one’s ability to adhere to the medications (four items), and health motivation or cue to action (four items). All items are scored on a Five-Point-Likert scale, i.e., strongly disagree (1 point), disagree (2 points), neutral (3 points), agree (4 points), and strongly agree (5 points). The score for each question will be summed up to determine the total scores. Higher scores indicate greater feelings related to that construct. All scales are positively related to screening behaviours except for barriers, which are negatively associated.

#### Quality of life

The abbreviated version of the World Health Organisation quality of life Questionnaire (WHOQoL-Bref) [27], that consists of 24 items will be used for assessing the participants’ quality of life perceptions in four domains, namely physical health, psychological health, social relationships, and environment within the previous 2 weeks.

With two other items being related to overall quality of life and general health. Scores in the domains are then converted into a linear scale from 0 to 100.

Other outcomes

#### Participantsʹ information

The sociodemographic profiles of the respondents will be assessed using five questions in the questionnaire (age, gender, marital status, educational level, and employment status).

#### Questionnaire and study module translation

The English version of the questionnaires used in this study will be translated using the forward translation and back-translation process. First, all questions are translated from English to Arabic according to the WHO process of translation and adaptation of instruments [28]. Then, the forward translation of the original questionnaire from English to Arabic will be performed by a certified linguistic translator (native speaker of Arabic and expert in English). Following that, back translation from Arabic to English will be done by another independent, qualified, and professional translator (native speaker of Arabic and expert in English). Finally, the back-translated English version is compared with the original questionnaire by another English language translator to ensure no discrepancy between items in the original and translated versions. The researcher then compares the translated version of the module and questionnaire with the original version to decide the accuracy of the final version of the module and questionnaire.

Subsequently, the translated module will be tried out on seven TB patients. It will also be face validated among ten TB patients. All these patients will be excluded in the subsequent randomised controlled trial (RCT). The participants will be asked individually about the clarity and comprehensibility of the questions. Phrases deemed unsuitable and/or hard to understand will then be modified accordingly. Correspondingly, the final version will be endorsed for use in the RCT.

### Statistical analysis

The data will be analysed using IBM SPSS Software 25.0 (SPSS Inc. Chicago, United States). Note that any missing data will be managed by adopting the intention‐to‐treat analysis concept. The continuous variables will be checked for normality prior to analysis. The value of p < 0.05 is set as the alpha level of significance. Baseline data will be outlined with descriptive analysis. For continuous variables, mean, standard deviation, median, and range will be used; frequency and percentage will be used for categorical variables. For the comparison of categorical data between groups, the chi‐square test will be used to compare the differences between the two groups. As for continuous data, an independent sample t‐test will be used. For the primary and secondary interests of analysis, multivariable regression model analysis will be employed to adjust confounding factors in the statistical effect. In addition, Cochran’s Q test will be used to assess the changes in categorical data in both groups over time. In contrast, continuous variables that change over time will be identified using one‐way repeated measures (ANOVA). After testing for assumptions and outliers, between-groups (intervention vs control), the main effect and interaction between and within the two groups over time will be tested using generalised estimating equations.

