### Sample size

The sample size is calculated using the standard sample size estimate for an individually randomised design. Sample size will be determined according to the primary dependent variable (TB treatment adherence). The formula to calculate the difference between two population proportions will be used (power = 0.80, alpha = 0.05 two‐sided, P_1_ = estimated proportion (larger) P1 = 0.82, P_2_ = estimated proportion (smaller) P2 = 0.69) [22].

$$N=\frac{\{1.96\sqrt{2\times 0.33(1-0.33)}+0.842\sqrt{0.82(1-0.82)+o69(1-0.69)}{\}}^{2}}{{\left(0.82-0.69\right)}^{2}}.$$

N = 171 for each group.

By taking into account a 10% attrition rate, a total sample size of 188 (171 + 17 = 188) participants will be required for each group, giving a total sample size of 376 participants.

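### The statistical section tests a GEE group main effect, a group-by-time interaction and within-arm changes without separating the term that estimates the treatment effect from those that do not

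*Protocol article*

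**What the plan says.** The protocol article measures adherence and the secondary scores at baseline, 1 month and 4 months. Under Study design, the educational material is given after the baseline data are collected; under Participant recruitment, the allocation envelope is opened after the baseline assessment.

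The Statistical analysis section then lists several analyses:

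- For categorical outcomes, Cochran's Q: "test will be used to assess the changes in categorical data in both groups over time".
- For continuous outcomes, "continuous variables that change over time will be identified using" one-way repeated-measures ANOVA.
- For the between-group comparison, "the main effect and interaction between and within the two groups over time will be tested using generalised estimating equations".
- Chi-square tests and t-tests between groups, and a multivariable regression with adjustment for confounders that are not listed.

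One significance rule covers all of them: "The value of p < 0.05 is set as the alpha level of significance". The abstract assigns GEE to the evaluation of change over time, and the closing objective in the Discussion lists baseline alongside the two follow-ups as a time point for assessing effectiveness. That baseline is one of the GEE's repeated outcomes is therefore implied, though never stated outright.

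**The concern.** The trial asks whether the intervention arm does better than the control arm after the intervention. Some of the listed tests answer that question and others do not, and the text treats them alike.

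- **Group main effect.** Because randomisation follows the baseline measurement, the expected baseline difference is zero. Averaging it with the two follow-up differences pulls the estimate towards zero. If the model also has the interaction and baseline is the reference visit, the group coefficient is the baseline difference alone and says nothing about the intervention.
- **Within-arm tests.** Cochran's Q and one-way repeated-measures ANOVA ask whether an arm changed over time. Patients on TB treatment may change in both arms for reasons unrelated to the education session. A significant change in one arm and a non-significant one in the other is not evidence of a difference between arms.

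A real effect could be understated or missed through the first route. An unsupported one could be claimed through the second.

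**Working it through.** **Inputs from the Sample size section.** "power = 0.80, alpha = 0.05", two-sided; "P1 = 0.82, P_2_ = estimated proportion (smaller) P2 = 0.69"; "N = 171 for each group", before the 10% attrition allowance.

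**Assumptions.** The article gives no within-patient correlation, so I take 0.5 with a range of 0.3 to 0.7, equal between all pairs of visits. Baseline adherence is 0.69 in both arms, and 0.82 v 0.69 holds at both follow-ups. Powers are normal approximations on the proportion scale.

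**1. The plan's own figure.** With pooled proportion (0.82 + 0.69)/2 = 0.755:

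n = (1.96 × √(2 × 0.755 × 0.245) + 0.842 × √(0.82 × 0.18 + 0.69 × 0.31))² / 0.13² = (1.96 × 0.6082 + 0.842 × 0.6012)² / 0.0169 = 170.7, so 171 per arm. It reproduces. (The 0.33 in the printed formula would give 194, and the abstract's 146 participants differ from this section's 376; both are separate matters.)

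**2. Dilution.** Mean of the three expected differences = (0 + 0.13 + 0.13)/3 = 0.0867, two thirds of 0.13.

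**3. Power at correlation 0.5.** Per-visit variances are 0.69 × 0.31 = 0.2139 (SD 0.4625) and 0.82 × 0.18 = 0.1476 (SD 0.3842).

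- *Main effect over three visits.* Variance of a patient's three-visit mean: intervention 0.1125, control 0.1426. SE = √((0.1125 + 0.1426)/171) = 0.0386. Power = Φ(0.0867/0.0386 − 1.96) = 61%.
- *Group-by-time contrast, 4 months minus baseline.* Variance of change: intervention 0.2139 + 0.1476 − 2 × 0.5 × 0.4625 × 0.3842 = 0.1838; control 2 × 0.2139 × 0.5 = 0.2139. SE = √(0.3977/171) = 0.0482. Power = Φ(0.13/0.0482 − 1.96) = 77%.
- *Baseline-adjusted difference at 4 months.* Variance (0.1476 + 0.2139) × (1 − 0.5²) = 0.2711. SE = √(0.2711/171) = 0.0398. Power = Φ(0.13/0.0398 − 1.96) = 90%.

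| Contrast | Expected value | Power, correlation 0.3 | 0.5 | 0.7 |
|---|---|---|---|---|
| Main effect, three visits | 0.087 | 71% | 61% | 54% |
| 4 months minus baseline, between arms | 0.13 | 63% | 77% | 93% |
| 4 months, unadjusted | 0.13 | 81% | 81% | 81% |
| 4 months, baseline-adjusted | 0.13 | 84% | 90% | 98% |

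Using one averaged variance for all visits and both arms instead gives 73/64/56% for the main effect and 67/81/95% for the change contrast. The conclusion is the same.

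**4. Simulation check.** Logistic GEE with exchangeable working correlation, 400 trials per scenario, latent correlation 0.3 and 0.6, true log odds ratio 0.716:

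- Main effect without interaction: mean 0.44 and 0.42.
- Group coefficient with interaction and baseline as reference: mean about 0, rejected in 4% to 5% of trials.
- Group-by-time term at 4 months: mean 0.70 and 0.74, power 60% and 76%.
- GEE with a common baseline: mean 0.71 and 0.73, power 80% and 86%.

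**5. Within-arm tests, if they were used to judge efficacy.** With no treatment effect and equal improvement in both arms, let each arm's test reject with probability q. The result significant in intervention and not in control then has probability q(1 − q): 21%, 25% and 16% for q = 0.3, 0.5 and 0.8. The nominal error in that direction is 2.5%. The maximum is 25%, at q = 0.5; the probability falls as the shared change becomes very small or very large.

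**The case against.** A reader might infer that the plan tests the wrong quantity altogether, so that the effect will be diluted or will be read off by comparing two within-arm p-values. The documents do not support that, for these reasons.

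- The GEE sentence names the interaction together with the main effect. With baseline among the outcomes, group-by-time is the between-arm difference in change, and it is not diluted. At correlation 0.5 its power is close to the planned 80%. At 0.3 it is lower than that of the main effect (63% v 71%), so the undiluted term is not always the more powerful.
- No section says that efficacy will be inferred from one arm changing significantly and the other not. The figures in step 5 describe what would follow from such a rule, not a rule that the article states.
- Between-group chi-square tests, t-tests and a multivariable regression are also listed. The regression's covariates are not given, which an article may leave to the full protocol or the analysis plan. It cannot be said that baseline adherence will go unadjusted.
- The statement about the group coefficient depends on coding: with 4 months as the reference visit, it would be the 4-month difference. Coding is not specified.
- When the intervention has no effect, the averaged main effect has expectation zero, so testing it does not inflate type I error. The harm is an understated effect and, in this setting, lower power than planned.

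All of this stands, and it limits the point to a risk. It does not remove the point: the article prescribes a main-effect test and within-arm tests at the same significance level as the valid contrast, with nothing to tell a reader which one answers the hypothesis.

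**Conclusion.** The point holds as a fault in how the analysis is laid out. Of the GEE terms and within-arm tests listed, only the group-by-time contrast estimates the treatment effect, and the text does not set it apart.

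If inference were drawn from a main effect that includes baseline, the expected estimate would be about two thirds of the planned difference and power about 61% (54% to 71%), not 80%. A baseline-adjusted difference at 4 months would have about 90% (84% to 98%) from the same patients.

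These sizes rest on 171 evaluable patients per arm, the planned 0.82 v 0.69 at both follow-ups, an assumed correlation of 0.3 to 0.7, and baseline being a repeated outcome in the GEE, which is well supported but inferred. The sizes would move with other inputs. That the main effect and the within-arm tests are not the treatment effect follows from the design and does not depend on the assumed correlation.

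**What to change.** Rewrite the GEE sentence so that between-arm inference comes from one model: the 1- and 4-month values as outcomes, with group, visit, group × visit and baseline MARS as terms. A close alternative keeps baseline as an outcome but constrains the arms to a common baseline mean and tests the group-by-visit contrast; it also uses patients who have only a baseline value.

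Report the between-arm difference with its confidence interval at the visit or visits that the sponsor designates as primary. The hypothesis covers both 1 and 4 months, so that choice belongs to the sponsor. If both are primary, say how the two tests share the 5% level.

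State that a group main effect that includes baseline is not used for inference. Label Cochran's Q and one-way repeated-measures ANOVA descriptive, or remove them. Use the same model form for the secondary scores, each with its own baseline value.

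The cost is a few sentences and one decision about the primary visit. Baseline MARS is already collected, so there are no new data and no change to the visits.

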## Results

The trial findings will be reported based on the Consolidated Standard of Reporting Trials (CONSORT) guidelines. In addition, the research outcomes will be published in an international peer-reviewed open-access journal. The principal investigator is responsible for disseminating the findings to Health facilities, Abu Anga hospital, the Ministry of Health (MOH), Universiti Putra Malaysia, and national and international conferences.

## Discussion

This study protocol outlined the use of a module to examine the effects of tuberculosis (TB) educational intervention on the adherence to TB treatment, knowledge, quality of life (QOL), and health beliefs of Sudanese TB patients in Khartoum state, Sudan using randomised controlled trial (RCT) design. Activities in the intervention have been formulated to be integrated into the routine practices of TB care to foster strong local ownership. A two-way interactive process between patients and physicians is fundamental to ensure adherence. There are many projected benefits from the RCT. It can generate information on the determinants of adherence to TB treatment and evaluate the barriers to reducing non-adherence. Non-adherence is the main challenge in the TB control program globally. As such, information from this RCT is vital to minimise treatment costs, guide policy direction, and improve patients’ QOL. The study findings can be implemented in tandem with the existing TB treatment strategy, such as Directly Observed Therapy (DOT).

To reduce the risk of non-adherence to TB treatment, healthcare workers must be trained to check patients’ adherence during home visits. A few limitations are likely to arise from the RCT. Firstly, the healthcare providers cannot be blinded, which may introduce performance bias. While reporting bias is also possible, it can be minimised by objectively and prospectively collecting the adherence history of patients. We will also ensure that the health workers provide equal care to patients in both groups, whereby the control group will also receive the educational module after the study.

In summary, this RCT will be useful in investigating the impact of TB educational intervention among Sudanese TB patients in Khartoum state, Sudan, especially on their adherence to TB treatment, TB knowledge, QOL, and health beliefs using an RCT design. The two objectives of this study are 1) developing an educational intervention based on the Health Belief Model (HBM) for TB treatment adherence, knowledge, life quality, and beliefs; assessing the effectiveness of the educational intervention on adherence to TB treatment, knowledge, QOL, and beliefs among Sudanese patients in Khartoum state, Sudan, at different time points (baseline, 1 month, and 4 months after intervention).
